#### **5.0 Data management and quality control**

At the end of each therapy session, the principle investigators (PI) will check the data recording forms for data recording errors and refer any need for amendment or completion of missing data back to the research assistants. Thereafter, the PI will complete coding of all relevant fields on the data recording forms. Data will then be double entered into a secure password protected

electronic database, excel sheet, checked for errors and cleaned. The final database will be exported into Statistical Package for Social Sciences (SPSS) software for analysis. All data collecting tools, with captured information, will be stored in lockable storage boxes, and will be accessed by the PIs only.

All research assistants will be qualified Physiotherapists who are providing care to patients at QECH; such personnel have background knowledge of the tools intended to be used in this study and have a background information on CR. In addition to this, they will be trained on how to efficiently and effectively use all tools. Therefore, standard operating procedures shall be developed and distributed to all assistants to ensure that they all execute the same functions exactly in the same manner throughout the implementation of the intervention and collection of data.

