### ***Specific Objectives:***

1. To describe improvements in cardiovascular function at rest and on exercise among patients with a diagnosis of CHF
2. To describe the frequency of hospitalization among patients diagnosed with CHF enrolled into the cardiovascular rehabilitation program (CRP).
3. To describe the challenges that may be associated with establishment of a CRP at the QECH.

**Study design, population, sample size and sampling strategy:** This will be a prospective open label clinical trial of patients being discharged from the medical wards at QECH with a diagnosis of CHF. There will be two arms in the study with a total of 80 participants; Arm 1 will comprise of 40 patients with CHF who will receive cardiovascular rehabilitation as an intervention of interest, along with the usual cardiac medications that also include secondary prevention drugs, while 40 patients with CHF in arm 2 will be on cardiac medications that also include secondary prevention medications and education but not the exercise component of cardiac rehabilitation. Each participant will pick unlabelled sealed envelope with a paper that has a number that will determine to which group he or she will belong to. Participants will be followed up for 24 weeks. Participants in arm 1 will have regular cardiovascular exercise training once a week for 12 weeks and followed up without active exercise training for another 12 weeks. Arm 2 participants shall receive education component of cardiac rehabilitation at baseline and during the time points they will come for screening. Participants in both arms 1 and 2 will

continue to take cardiac medications as per their cardiologist's prescription throughout the study period.

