## 4.0 Methodology

### 4.1 Design

The study shall use a prospective open label clinical trial design, and quantitative methods will be employed.

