#### **4.7 Data Collection**

A manual sphygmomanometer will be used to measure BP, Oximeter will be used to measure Oxygen saturations. PR will be checked manually by feeling the radial artery using the third and index fingers Risk stratification will be done using the BACPR stratification forms (Appendices 1-2). Exercise testing will be conducted using **Chester step test for prescription (Appendix 9)**, and **exertion tolerance capacity will be checked using 6-minute walk test**; more details on 6-minute walk test can be accessed using this link (<https://doi.org/10.1164/ajrccm.166.1.at1102>) (24), and outcomes of 6-minute walk test will be recorded using the form attached as an appendix (Appendix 3).

As aforementioned, patients will be screened at baseline before being enrolled into the CRP. At baseline, the following descriptive data will be collected; BP, PR, O2sats and exercise capacity.

Additionally, data on risk stratification for disease progression and occurrence of cardiac events during exercise therapy will be recorded at baseline. BP and PR will be checked before and after each session for safety purposes **(Appendix 12)**; patients will also be asked, on each hospital therapy day, about the challenges faced that may be negatively contributing to adherence of the home exercise and nutrition interventional advice given to be followed at home. All parameters, including incidents of hospital admissions, will also be examined and recorded at 4, 8, 12, 16 and 24 weeks. **The Physiotherapists will record challenges they experienced at all stages of this project; from enrolment of study participants to discharge (Appendix 11).** The data will be collected on paper, and transferred onto Microsoft excel sheet on a computer.

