## **10.0 Requirements, timeline of events and budget**

**Table 2:** Required items for the execution of this study

| ITEM                                                                                       | ROLE/USE                                                                                                                                                                                                                                                                                                                                                                                                                  |
|--------------------------------------------------------------------------------------------|---------------------------------------------------------------------------------------------------------------------------------------------------------------------------------------------------------------------------------------------------------------------------------------------------------------------------------------------------------------------------------------------------------------------------|
| PERSONNEL: Physiotherapist
Cardiologist/physician
Statistician
Patients' guardian | To assess and deliver the intervention package
To refer patients for enrollment and respond to all relevant medical queries
To assist with data management and analysis
To guide and monitor home exercise treatment                                                                                                                                                                                             |
| Training: Physiotherapists & chest
medical team

Patients' guardian               | Briefing on the objectives of the study, the inclusion and exclusion criteria, the intervention package and their responsibilities. Testing the tools and intervention to evaluate the capacity of the health care workers to function effectively towards this study.

To equip them with knowledge and skills on how they can effectively guide and monitor a 2-day home exercise program every week for 12 weeks |

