|           | Physiotherapists       | 4        | MK20,000/individual/session for 12 sessions            | MK960,000       | \$1280          | For enrollment, screening and implementation. Two therapists will be needed to conduct assessments on all patients during the follow up period at 16 and 24 weeks after the implementation period |
|           |                        | 2        | MK20,000/individual/session for 2 extra patient visits | MK40,000        | \$53.3          |                                                                                                                                                                                                   |
|           | Statistician           | 1        | MK20,000/day for 10 days                               | MK200,000       | \$266.67        | To assist with data management                                                                                                                                                                    |

|           |                  |                                |                                  |               |              |                                                                                                      |
|-----------|------------------|--------------------------------|----------------------------------|---------------|--------------|------------------------------------------------------------------------------------------------------|
| EQUIPMENT | sphygmomanometer | 3                              | MK30,000                         | MK90,000      | \$120        | 15 boxes will be given to the patients for home exercise program and 16 will be used at the hospital |
|           | Stethoscope      | 3                              | MK45,000                         | MK135,000     | \$180        |                                                                                                      |
|           | Dumbbells        | 18 pairs                       | MK12,000 a pair                  | MK 96,000     | \$128        |                                                                                                      |
|           | Stepping boxes   | 31                             | MK 17,000 a box                  | MK 527,000    | \$702.67     |                                                                                                      |

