#### Appendix 4: Cardio-respiratory parameters

**ID:**

**Initials:**

| PARAMETERS                                           | BASELINE | 4 WEEKS | 8 WEEKS | 12 WEEKS | 16 WEEKS | 24 WEEKS |
|------------------------------------------------------|----------|---------|---------|----------|----------|----------|
| Blood Pressure                                       |          |         |         |          |          |          |
| Heart Rate                                           |          |         |         |          |          |          |
| O 2 sats                                  |          |         |         |          |          |          |
| Exercise tolerance capacity                          |          |         |         |          |          |          |
| Challenges                                           |          |         |         |          |          |          |
| Number of hospital admissions (reason for admission) |          |         |         |          |          |          |

PATIENT ID:.....

HR AT REST.....

BETA-BLOCKED?:.....

HRMAX:.....

HRR:.....

70%HRR:.....

| STAGES | HEART RATE | METS
ACHIEVED | OXYGEN
SATURATION | RPE |
|--------|------------|------------------|----------------------|-----|
| 1      |            |                  |                      |     |
| 2      |            |                  |                      |     |
| 3      |            |                  |                      |     |
| 4      |            |                  |                      |     |
| 5      |            |                  |                      |     |

TEST COMPLETED? YES NO

REASON FOR TERMINATION:.....  
 .....  
 .....  
 .....

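### Open-label trial with no independent or masked assessor: blood pressure, pulse and walk distance could be measured in favour of Arm 1, and cheap protection is left unused

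*Protocol*

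**What the plan says.** Section 4.1 fixes the design: "The study shall use a prospective open label clinical trial design, and quantitative methods will be employed". The executive summary adds: "There will be two arms in the study with a total of 80 participants", that is, 40 per arm.

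**Who measures.** Section 5.0 says: "All research assistants will be qualified Physiotherapists who are providing care to patients at QECH". Standard operating procedures are to make these assistants work "exactly in the same manner throughout the implementation of the intervention and collection of data". Table 2 (section 10.0) gives the physiotherapist's role as "To assess and deliver the intervention package". Table 4 pays four physiotherapists to enrol, screen and run the programme, and continues: "Two therapists will be needed to conduct assessments on all patients during the follow up period at 16 and 24 weeks". Nothing says that those two must be independent of the weekly sessions, and the assessors at weeks 4, 8 and 12 are not named. Masked assessment is not mentioned.

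**How.** Under section 4.7, blood pressure is taken with a manual sphygmomanometer and exercise tolerance with the 6-minute walk test. For pulse, "PR will be checked manually by feeling the radial artery" is the method. Saturation is read from an oximeter.

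**On what form.** Appendix 4 is one sheet per patient with columns for baseline and weeks 4, 8, 12, 16 and 24. Its rows are blood pressure, heart rate, saturation, exercise tolerance capacity, Challenges and admissions. The walk test also has its own single-test form, Appendix 3.

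**The concern.** Patients and therapists cannot be blinded to exercise training. Measurement is where protection remains possible, and the protocol provides little of it. A physiotherapist who has worked with the Arm 1 patients and expects them to improve (the executive summary states that expectation) may encourage harder during the walk. The same person may round a manual reading or a counted pulse in the hoped-for direction, and having the last value on the same page makes that easier.

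The resulting error would be systematic and would differ between arms. The independent t-test in section 6.0 would count it as a treatment effect. Section 2.0 intends the results to inform national guidelines and scale-up to other hospitals, so a spurious difference would matter beyond this pilot.

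**Working it through.** **1. Overlap of treatment and measurement.** Four statements are read together:
- Section 5.0: the assistants are care-giving physiotherapists, and one set of procedures covers both delivery and data collection.
- Table 2: physiotherapists assess and deliver.
- Table 4: therapists carry out the late assessments, with no independence condition.
- Section 4.4: the hospital's physiotherapy department takes part in delivering care at the gym.

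Overlap is therefore permitted and likely. No sentence says that a given therapist measures the patients whom he or she trained.

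**2. Which outcomes are exposed.**
- Blood pressure (manual) and pulse (palpated): observer-dependent.
- Walk distance: effort-dependent. The amendment request at the front of the protocol itself says that more than one person is needed for accurate walk-test results.
- Saturation (oximeter) and admissions: less exposed.

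**3. What the form shows.** In Appendix 4, earlier blood pressure and heart rate values lie next to the current cell. Walk distance is first written on Appendix 3, which carries one date and no earlier result, and then appears as exercise tolerance capacity in Appendix 4.

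**4. Size, as illustration only.** The plan gives no figure for assessor bias. Its only design figure is 40 per arm (section 4.4). That figure does not follow from its stated inputs. A two-sided 5% test at 80% power needs n = 2(1.96 + 0.84)²/d²:
- d = 0.6: 15.68/0.36 = 43.6, so 44 per arm.
- d = 0.6/1.2 = 0.5: 15.68/0.25 = 62.7, so 63 per arm.

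That is a separate matter, and 40 is used below as the planned size.

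In SD units, the standard error of the difference is √(2/40) = 0.2236. With no true effect and an assumed shift b towards Arm 1, the two-sided 5% rejection rate (normal approximation) is P(Z > 1.96 − b/0.2236) + P(Z < −1.96 − b/0.2236).

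| Assumed b (SD) | b/SE | Upper tail | Lower tail | False-positive rate |
|---|---|---|---|---|
| 0.10 | 0.447 | P(Z > 1.513) = 0.065 | P(Z < −2.407) = 0.008 | 7.3% |
| 0.25 | 1.118 | P(Z > 0.842) = 0.200 | P(Z < −3.078) = 0.001 | 20.1% |

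The planned effect of 0.6 can be read as 0.6 SD, or as 0.6/1.2 = 0.5 SD. A shift of 0.1 SD is then 17% or 20% of it, and 0.25 SD is 42% or 50%.

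**5. Visit schedule.** Section 4.5 brings Arm 2 in at baseline and weeks 4, 8, 12 and 24. Section 4.7 and Appendix 4 also have week 16, and Table 4 has all patients assessed then. These passages contradict each other.

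**The case against.** A reader might infer more than the documents support.

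- **That each therapist measures his or her own trainees.** This is not stated. Section 5.0 speaks of care to patients at the hospital in general. The point rests on the absence of any separation.
- **That the week-12 assessor sees all earlier results.** The text does not say whether Appendix 4 is filled in at the visit or compiled later, and Appendix 3 already isolates the walk test. Section 5.0 locks completed forms away for the investigators only. However, section 8.0 gives the treating therapists access to the data, and a running sheet has to be reopened for each new entry. The concern about sight of earlier values stands for blood pressure and pulse, as a risk.
- **That the Challenges row identifies the arm.** Section 4.7 ties it to home exercise, which only Arm 1 is prescribed, but also to nutrition advice, and Arm 2 receives nutrition education. It may hint at the arm but need not reveal it.
- **That walk-test encouragement is unstandardised.** Section 4.7 cites a walk-test guideline and section 5.0 promises standard operating procedures. Neither can be seen here, so absence cannot be claimed.

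Two further objections carry weight. This is a pilot with descriptive objectives, which lowers the stakes of a false positive. A change of assessor at weeks 16 and 24 also leaves week 12 untouched, and that is one of the two follow-up points compared in section 6.0. A therapist who ran the sessions will know the arm, and the readings in Appendix 12, whatever Appendix 4 looks like. The form change therefore helps most when someone else measures.

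**Conclusion.** The point holds as a risk. In an open-label trial, the protocol gives physiotherapists both delivery and assessment and names no independent or masked assessor. Blood pressure, pulse and walk distance could therefore be measured in favour of Arm 1. For blood pressure and pulse, the layout of Appendix 4 adds to this. Training, procedures, form checks and double entry address consistency and transcription, but not knowledge of the arm.

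The bias cannot be sized from the documents. The false-positive rates of about 7% and 20% rest on assumed shifts of 0.1 and 0.25 SD, 40 analysed per arm and a normal approximation. They show what such a shift would do and do not predict that it will occur. This is a worthwhile low-cost improvement, and the point does not show that the results would be invalid.

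**What to change.** With existing resources:

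1. Replace the running Appendix 4 with one sheet per visit that shows no earlier values. Move Challenges to a separate form completed after the measurements.
2. State that the two therapists listed for the week 16 and 24 assessments are physiotherapists who did not run the Arm 1 sessions. At week 12, roster available staff where possible so that the person measuring is not the one who supervised that patient.
3. State in the standard operating procedure that the same walk-test encouragement is used in both arms.
4. Acknowledge unmasked assessment as a limitation, particularly at week 12.
5. Reconcile section 4.5 with section 4.7, Appendix 4 and Table 4 on whether Arm 2 attends at week 16.

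Recording an oximeter pulse beside the palpated one is not recommended unless the device displays pulse and the plan says which value is analysed.

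The cost is reprinted forms, a line in the procedure, more sheets to file and less rostering freedom. No new post is needed. The Table 4 line for the two therapists should be checked, however: 2 × MK20,000 × 2 visits = MK80,000, against MK40,000 shown.

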## **6.0 Analysis and presentation of results**

The SPSS software will be used to analyze this data. Frequencies and mean changes with standard deviations will be used to descriptively illustrate the effect size of the intervention. Paired t-tests will be carried out to compare and show the changes in the variables at the start of the program and after 3 and 6 months of CR reception. **Independent t-tests will be carried out to compare results between the two groups.** Tables and graphs will be used to present the findings.

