**Exclusion criteria**

- a. Failure to provide informed consent form
- b. Not willing to return for follow up visits
- c. Physical impairment that would affect participation in physical activity
- d. Coming from outside Blantyre
- e. Patients classified as high risk for cardiac events during exertion

**Data management and analysis:** Descriptive analysis will be conducted using SPSS software; frequencies and mean changes with standard deviations and confidence intervals will be used to report the effect size of the intervention. Multivariate paired T tests will be conducted to compare the changes in each variable at the five time points, and **independent t-test will be conducted to compare the changes between the two groups.** Tables and graphs will be used to present the findings.

Expected outcomes: Participants in arm 1 will have better cardiovascular function and fewer hospital admission compared with the controls during the first 12 weeks and that these benefits will remain at 24 weeks.

**Dissemination plans:** Findings from the study will be presented to QECH management and clinicians involved in managing patients with CHF. The findings will also be presented at the COMREC dissemination conference. Furthermore, the results will be submitted to a peer review journal for publication.

***Anticipated challenges:*** It is anticipated that patients may be lost to follow up and discontinue with the prescribed intervention due to transportation related costs. Therefore, the patients enrolled in this program will be assisted with the transportation costs; patients enrolled will be those who will manage to travel the distance with the allowance given. In addition, patients will be asked to come for a therapy session at the hospital once each week and do the other two sessions at home with a trained family member.

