#### 4.31 Inclusion criteria

- a. Men and women 18 years and above with a diagnosis of CHF at discharge from hospital, confirmed with an echocardiogram
- b. Being residents of Blantyre City and its immediate surrounding areas
- c. Willing to provide written informed consent and willing to return for follow up
- d. Being able to participate in physical activity for cardiac rehabilitation

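### The effect size is attached to mean changes and paired t-tests, and the planned between-arm comparison is not named as the effect estimate

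*Protocol*

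**What the plan says.** Two places in the protocol describe the analysis.

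- **Section 6.0** says: "Frequencies and mean changes with standard deviations will be used to descriptively illustrate the effect size of the intervention". It continues: "Paired t-tests will be carried out to compare and show the changes in the variables at the start of the program", with the later measurements at 3 and 6 months. It then adds: "Independent t-tests will be carried out to compare results between the two groups".
- **The executive summary**, under data management and analysis, says: "frequencies and mean changes with standard deviations and confidence intervals will be used to report the effect size of the intervention". It adds: "Multivariate paired T tests will be conducted to compare the changes in each variable at the five time points". It also plans an independent t-test, there applied to changes rather than results.

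The amendment letter records that the independent t-test was added because it had been missed. The sentences on effect size carry no reference to it.

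Elsewhere the protocol thinks in terms of a contrast between arms. Section 4.4 bases the sample size on an effect of 0.6, which it explains as a between-group difference. The expected outcomes in the executive summary are better function and fewer admissions in Arm 1 than in Arm 2. Specific objectives 1 and 2 name no comparator.

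Admissions are to be recorded at 4, 8, 12, 16 and 24 weeks (section 4.7). The Appendix 4 form has a row headed "Number of hospital admissions (reason for admission)" with a column for each of those visits and one for baseline.

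**The concern.** In a randomised two-arm trial, the effect of the intervention is the difference between arms. A mean change over time, or a paired test of it, measures everything that happens to patients between two visits. Here that could include recovery after an admission, continuing cardiac medication, the education given to both arms, familiarity with a repeated walk test, and regression to the mean.

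The label that will head the results, the effect size of the intervention, is attached to the mean changes. The quantity the trial was sized on appears as a further test with no stated rank. A before-and-after gain in Arm 1 could then be reported as the effect of rehabilitation. Section 2.0 wants the findings to inform management guidelines and roll-out to other hospitals, so the distinction matters.

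Admissions raise a related problem. The only tests named anywhere are t-tests, which suit a count that may be zero for many patients poorly.

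**Working it through.** **The plan's own figure.** The protocol gives no expected change over time, so there is no within-arm figure to reproduce. Its one statistical figure is 40 per arm for a between-group effect of 0.6 (section 4.4). I take 40 per arm as given. Whether it follows from its stated inputs is a separate matter that does not affect this point.

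**Inputs**
- From section 4.4: n = 40 per arm, two-sided 5% level, 5% dropout (40 × 0.95 = 38).
- Assumed, because the documents are silent: a common improvement c of 0 to 0.6 baseline SD in both arms; correlation r between baseline and follow-up of 0.5 or 0.7; normal data with equal SD at both times; no rehabilitation effect.

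**Formulas.** In baseline SD units, the SD of change is √(2(1 − r)): 1.00 at r = 0.5 and √0.6 = 0.77 at r = 0.7. The paired test in Arm 1 has non-centrality c√n / SD of change, which grows with c. The between-arm test on change has expected difference c − c = 0 whatever c is, so it should keep its 5% level.

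**Results** (20,000 simulated trials per row, n = 40 per arm)

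| c | Arm 1 paired test significant: r = 0.5 / 0.7 | Arm 1 significant, Arm 2 not: r = 0.5 / 0.7 | Between-arm test on change significant: r = 0.5 / 0.7 |
|---|---|---|---|
| 0 | 5% / 5% | 5% / 5% | 5.1% / 5.3% |
| 0.2 | 24% / 36% | 18% / 23% | 5.0% / 4.9% |
| 0.3 | 46% / 66% | 25% / 22% | 5.0% / 4.8% |
| 0.5 | 87% / 98% | 11% / 2% | 4.8% / 5.0% |
| 0.6 | 96% / 99.8% | 4% / 0.2% | 5.0% / 4.9% |

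Direct power calculation agrees at r = 0.5: 0.457 at c = 0.3 and 0.869 at c = 0.5. For identical arms, the chance that Arm 1 is significant and Arm 2 is not is p(1 − p); at c = 0.3 this is 0.457 × 0.543 = 0.248. With 38 per arm and r = 0.5, the paired test runs from 22% to 95% over c = 0.2 to 0.6, and the between-arm test from 4.5% to 5.1%.

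**Change score or baseline adjustment.** Under the same assumptions, the outcome variance is 2(1 − r) for a change score and 1 − r² after adjustment for baseline. At r = 0.5 that is 1.00 against 0.75; at r = 0.7 it is 0.60 against 0.51. Adjustment therefore estimates the same contrast more precisely.

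**Admissions.** Setting the passages side by side: section 4.7 counts admissions among the parameters recorded at follow-up; the executive summary applies paired tests to each variable; Appendix 4 has a baseline cell for admissions with no look-back period. Together these permit a paired comparison of admissions with baseline, though none is named. Section 4.31 requires patients "with a diagnosis of CHF at discharge from hospital". If the baseline cell captured that index admission, a fall would be built in.

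**The case against.** The strongest reply is that the randomised comparison is already planned. Section 6.0 compares the two groups, the executive summary compares their changes, and the amendment added this test deliberately. On the same assumptions it holds its level at about 5%. Section 6.0 also calls the mean changes descriptive, and neither place says they are for one arm only. All of this stands. It limits the point to which quantity is called the effect and what rank the tests have.

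Three stronger readings are tempting, and the documents do not support them.

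- A reader might infer that the effect rests only on within-arm analyses. The independent t-tests contradict that.
- A reader might infer that the plan will treat a significant Arm 1 and a non-significant Arm 2 as proof of benefit. No sentence proposes that; the corresponding column above shows only what such a reading would risk.
- A reader might infer that admissions must fall by construction. That needs a baseline of one for every patient. Section 4.7 does not list admissions among the baseline data, Appendix 4 gives no look-back period, and section 4.3 describes patients attending clinic follow-up, so recent discharge is not settled. A simulation that fixes the baseline at one would only return its own assumption.

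A fair reply is also that the choice of count model can be left to an analysis plan. What remains is that the protocol names t-tests and nothing else.

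**Conclusion.** The point holds as a defect in how the effect is defined. Both descriptions attach the effect size to mean changes and give paired tests at least equal standing, while section 4.4 sizes the trial on a between-group difference. They also disagree on whether the between-arm test compares results or changes.

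If both arms improve by 0.2 to 0.6 SD with no rehabilitation effect, the Arm 1 paired test is significant in about 24% to 96% of trials at r = 0.5, and in 36% to 99.8% at r = 0.7. The between-arm test on change stays near 5%. These ranges rest on assumed improvements and correlations; with no common improvement, the paired test also stays at 5%. The direction does not depend on the exact values: any shared improvement inflates the paired test and leaves the between-arm test alone.

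For admissions, the conclusion is narrower: t-tests are the only tests named for a count, and the baseline cell is not safe to use in a change score.

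**What to change.** In section 6.0 and in the executive summary, state that the effect size is the Arm 1 minus Arm 2 difference in change, preferably baseline-adjusted, with a 95% confidence interval at 12 and 24 weeks. Use the same wording in both places, which also removes the mismatch between results and changes. Keep mean change with SD by arm as description, without within-arm p-values.

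For admissions, count those recorded after allocation. Compare the arms by a rate ratio with an exact or Poisson/negative-binomial confidence interval, and by the proportion of patients with at least one admission. Take follow-up time to the last attended visit, because the Appendix 4 form records number and reason but no dates. Do not use the baseline admissions cell in a change score.

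The cost is the loss of the within-arm p-values and an approximate person-time denominator. This is a wording change that uses measurements already planned.
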